## Abstract

**Background:**

Increasing prevalence of obesity and disorders associated with sedentary living constitute a major global public health problem. While previous evaluations of interventions to increase physical activity have involved communities or individuals with established disease, less attention has been given to interventions for individuals at risk of disease.

**Methods/design:**

***ProActive ***aims to evaluate the efficacy of a theoretical, evidence- and family-based intervention programme to increase physical activity in a sedentary population, defined as being at-risk through having a parental family history of diabetes. Primary care diabetes or family history registers were used to recruit 365 individuals aged 30–50 years, screened for activity level. Participants were assigned by central randomisation to three intervention programmes: brief written advice (comparison group), or a psychologically based behavioural change programme, delivered either by telephone (distance group) or face-to-face in the family home over one year. The protocol-driven intervention programme is delivered by trained facilitators, and aims to support increases in physical activity through the introduction and facilitation of a range of self-regulatory skills (e.g. goal setting). The primary outcome is daytime energy expenditure and its ratio to resting energy expenditure, measured at baseline and one year using individually calibrated heart rate monitoring. Secondary measures include self-report of individual and family activity, psychological mediators of behaviour change, physiological and biochemical correlates, acceptability, and costs, measured at baseline, six months and one year. The primary intention to treat analysis will compare groups at one-year post randomisation. Estimation of the impact on diabetes incidence will be modelled using data from a parallel ten-year cohort study using similar measures.

**Discussion:**

***ProActive ***is the first efficacy trial of an intervention programme to promote physical activity in a defined high-risk group accessible through primary care. The intervention programme is based on psychological theory and evidence; it introduces and facilitates the use of self-regulatory skills to support behaviour change and maintenance. The trial addresses a range of methodological weaknesses in the field by careful specification and quality assurance of the intervention programme, precise characterisation of participants, year-long follow-up and objective measurement of physical activity. Due to report in 2005, ***ProActive ***will provide estimates of the extent to which this approach could assist at-risk groups who could benefit from changes in behaviours affecting health, and inform future pragmatic trials.

## Background

This trial addresses the rise in the burden of disease associated with sedentary living: a major public health problem. Physical inactivity accounts for up to 11.7% of all deaths in developed countries [1] and it has been causally associated with coronary heart disease, diabetes, osteoporosis and some cancers. The rise in the prevalence of obesity in many countries may be associated with a decline in physical activity.

Reversal of this trend will require not only public health programmes to increase activity at societal level, but also interventions to help high-risk individuals increase physical activity and maintain beneficial activity patterns [2]. This is a trial of such an intervention. It aims to overcome the limitations of previous studies through careful choice and characterisation of the target population, study design, measures, and the interventions under evaluation themselves. The intervention programme, based on theories and evidence from psychology about how best to support behavioural change and maintenance, is potentially generalisable to other settings, target groups and behaviours.

### Target population

The study targets people with a parental family history of Type 2 diabetes and a sedentary lifestyle, who constitute a clearly identifiable high-risk population [3]. A consistent direct relationship exists between sedentary living and Type 2 diabetes [3,4]. People with a family history of diabetes have a three-fold increased risk of developing diabetes compared to those without; a risk that is magnified by physical inactivity and weight gain [3,5]. At least 40% of the excess risk associated with weight gain might be avoided in such people if their BMI did not exceed 30 kg/m^2 ^[2,3], and prospective studies support the idea that physical activity reduces weight gain [5,6].

### Limitations of previous trials

Most trials have evaluated increasing physical activity in the context of established disease. The few published trials of primary prevention in high-risk groups have methodological limitations. They have mainly evaluated brief interventions to increase exercise in the general population delivered through primary care practitioners [7-9], often with very short follow-up (a few weeks). Those such as the Activity Counselling Trial ("ACT"), offering follow-up for two years, are based on an unknown proportion of willing attendees at ambulatory care facilities [10,11]. Evaluation of exercise prescriptions delivered through leisure centres has not been encouraging [12]. Moreover, participants have been poorly characterised in terms of risk, and most studies have relied on self-reports of exercise. This may inflate differences between groups due to recall bias, and cannot capture changes in either total energy expenditure, or physical activity related energy expenditure [13]. Measuring total energy expenditure is relevant if an increase in one component of activity results in a decline in another, as activities are substituted, and measuring physical activity related energy expenditure (i.e. total energy expenditure adjusted for resting energy expenditure) is important if this is the aetiologically relevant factor.

Three trials among individuals with impaired glucose tolerance in China [14], Finland [15] and USA [16], have established that intensive approaches to lifestyle changes including physical activity can delay progression to diabetes by 58% over three years [15,16] and possibly longer [14]. Few studies have modelled the long-term effects of physical activity, although available work suggests that interventions for primary prevention of Type 2 diabetes might be cost-effective [17]. A full review of primary prevention trials [5] identified no interventions aimed at increasing physical activity alone, without accompanying dietary change or intended weight loss. The current study addresses this gap, and previous methodological shortcomings, by careful characterisation of the participants, year-long follow-up, objective measurement of physical activity, and modelling of the relationship between current behaviour change and future disease risk.

### Limitations of previous interventions

#### (i) Poorly specified interventions

Many of the available trials evaluated interventions that were not explicitly based on psychological theory and evidence, and did not specify clearly which behaviour change techniques were applied by the providers [18-20]. In addition, interventions often used relatively ineffective behaviour change techniques, for instance giving people advice about behaviour change [21,22]. More effective interventions to promote physical activity have applied psychological theory and evidence about how best to support behaviour change [16,23]. The development of the ***ProActive ***intervention programme included a review of psychological theories and evidence, through systematic reviews [18,20] and expert meetings, and a one-year feasibility study among 15 willing participants and their families. Based on this work, the Theory of Planned Behaviour (TPB) [24] was selected as the theoretical framework to inform behavioural determinants targeted in the intervention. Determinants include beliefs and attitudes towards the behaviour (here physical activity), which are elicited at an individual level. Tailoring interventions to personal beliefs is an innovative, but theoretically appropriate application of the TPB. Systematic reviews and expert meetings then informed the selection of potentially effective techniques aimed at changing beliefs. They include reinforcement of positive beliefs, and problem solving in relation to negative beliefs, in order to strengthen motivation.

#### (ii) Attention to adoption and maintenance of physical activity

A range of behaviour change techniques with evidence for their effectiveness was used to bridge the gap between intention and action: goal setting and review, action planning, use of prompts, self-monitoring, and reinforcement [2,18,23,25]. Use of a causal model, linking measured beliefs and attitudes to behaviour will allow subsequent process analysis to better specify both determinants and intervention (Hardeman *et al*., 2004. A causal modelling approach to the development of theory-based behaviour change programmes for trial evaluation. Submitted).

Major challenges in promoting physical activity are maintenance of behaviour change, and the avoidance of drop out rates that can approach 50% [5,26]. Reviews suggest that theoretical advances in facilitating behaviour maintenance have not been applied in intervention programmes [27,28]. The highest levels of participation have been achieved by home-based interventions, involving frequent professional contact, and promoting enjoyable, informal exercise of moderate intensity, such as walking [2,8]. Behavioural maintenance may be best supported by building habits, using self-regulatory strategies such as repetition of behaviours over time in a constant environment, ongoing goal review, self-monitoring, reinforcement, and relapse prevention [28,29]. The use of mail and telephone contacts is a promising cost-effective approach [23], especially the use of frequent, brief, support calls [2]. All these approaches are incorporated into ***ProActive***.

### ProActive objectives

The primary objective of ***ProActive ***is to determine the effects of a theoretical- and evidence-based intervention programme on objectively measured physical activity after one year, in sedentary individuals at risk of diabetes and related metabolic abnormalities due to their family history. Three questions are posed:

1. Behaviour change: Can an innovative approach to increasing physical activity achieve clinically important change in this behaviour when offered to a group at increased risk of diabetes?

2. Disease impact: If so, what is the potential for the changes in behaviour achieved in mid-life to reduce the incidence of diabetes in later life?

3. Dose finding: How does delivery of the approach, at two levels of intensity, affect acceptability, efficacy and costs?

The trial will estimate the extent to which physical activity and its key psychological mediators are altered by the intervention programme, and assess its acceptability to this high-risk group. It will document the extent to which behaviour change is associated with reduction in weight gain and improvement in physiological and biochemical correlates, and will model the potential impact of the intervention on future risk of diabetes.

Intensive, face-to-face interventions may not be a feasible health service model, and there is some evidence that less intensive, continuous support may be as effective [2,23]. The intervention programme is therefore being evaluated at two levels of intensity: 'face-to-face' (delivered at the participants' homes and by telephone) and 'distance' (delivered by one home visit and telephone and correspondence) over one year, in order to inform the most cost-effective intervention programme for wider evaluation. If potential efficacy is demonstrated, we intend to proceed to a multi-centre pragmatic trial of the cost-effectiveness of the approach in practice.

## Methods/design

***ProActive ***is a four-year study with a complex randomised trial design [30], with central randomisation of willing participants to intervention programmes or comparison. The trial is managed from the Institute of Public Health, University of Cambridge, following MRC guidelines. Ethical approval has been obtained from the Eastern MREC, and West Suffolk, Cambridge, Huntingdon and West Essex LRECs.

The study design and patient flows (achieved at recruitment closure, October 2003, and projected to end of study) are shown in Figure 1. The focus of measurement is the adult offspring of a Type 2 diabetic parent, but the focus of the intervention programme is this individual within a family context. Participants were recruited via parents with diabetes on primary care registers (20 practices), or directly through records of their family history of diabetes (seven of the 20 practices). Sedentary individuals and their families were randomised to facilitation, either 'face-to-face' or 'distance', or to a comparison arm offering a leaflet providing brief advice on the benefits of activity. Psychological, physiological, anthropometric and biochemical data were collected at baseline and one year after randomisation, with psychological data also collected at six months after randomisation.

**Figure 1 F1:**
[figure not shown]
Trial design and patient flows; Oct 2003 (recruitment closure)

The study is explanatory in design, and the quality-assured intervention programmes are delivered by carefully trained and supervised family health facilitators with experience of working in primary care or the community, and backgrounds in health promotion, dietetics and nursing.

### Setting, recruitment and screening

The study is set in urban, suburban and rural Cambridgeshire, Essex and West Suffolk, England, in the homes of participants and their families. The study population consists of offspring of people with Type 2 diabetes, aged 30–50 years, without a diagnosis of diabetes, and not considered very active based on self-report at the start of the study (see below). This age range defines a group at risk of weight gain [31,32]. Any individuals found at study entry to have fasting hyperglycaemia [33] were referred to their family doctor, but retained in the trial.

### Practice recruitment

Once the relevant ethical and PCT approval had been obtained, 53 practice teams in the locality were approached by letter, inviting them to take part in the study, and highlighting the reimbursement of all costs involved. Personalised letters were sent to the practice manager (who we asked to collate responses and reply using a reply slip and Freepost envelope), all partners and nursing staff. Included with each letter was a brief summary of the study and a Research Information Sheet for Practices (RISP) form [34]. If no response was received, a follow-up phone call was made to the practice manager. A principal investigator and member of the trial team visited interested practice teams, to discuss the study in further detail. All relevant practice staff were encouraged to attend, particularly those who would be involved in the administration of proposed patient surveys. The 20 practices that agreed to take part then received a 'set-up' visit by the trial team. A 'Practice Survey Manual' was created for the practice staff, and the trial team supported the practice teams as needed throughout the survey period.

### Participant recruitment

Initially participants were recruited through their parents; patients with Type 2 diabetes on the diabetes registers of 20 practices ('recruitment method 1'). Patients were written to by their general practitioner, with a description of the study, and asked to provide contact information for any offspring aged 30–50 years, living locally. Consent was also sought for the practice to pass the contact details of the offspring to the research team so that they could invite the offspring directly into the study. Piloting demonstrated feasibility and acceptability of the method, and one reminder was sent after three weeks if no reply was received.

From 20 practices, 2631 patients were approached and 2025 (77%) replied, yielding 1238 potentially eligible offspring who were invited to take part in the study. The ratio of approximately one potentially eligible offspring to two patients with diabetes was half our pilot projections, so to increase recruitment we developed a second recruitment approach ('recruitment method 2'). This approach recruited potential participants with a recorded family history of diabetes directly from practices with family history registers, and was feasible in seven of the 20 practices. General practitioners wrote to all patients aged 30–50 years with a recorded family history of diabetes, enclosing a study information sheet, and asking those willing to complete and return to the practice a questionnaire to determine which family member(s) had diabetes, and of which type. Consent was sought for this information and contact details to be passed on to the research team. Using this method, with again one reminder letter, 1340 patients were written to, and 896 (67%) responses were received, with 283 patients interested and eligible. Both recruitment approaches provided 1521 potential trial participants. Practitioners used their discretion in applying both approaches to the exclusion of patients who were physically or mentally unwell.

### Study population: inclusion and exclusion criteria

#### Activity levels

Potential participants recruited by both methods were next written to by the research team with full information about the study and a screening activity questionnaire, describing occupational and leisure activity, based on published questionnaires [35,36], to exclude very active individuals. Two reminder letters with questionnaires were sent at two-week intervals if necessary, giving a response rate of 74%. Respondents were excluded if they reported their occupational activity as 'heavy manual work' [35]; or 'physical work' if their total score on the leisure questionnaire [36] was ≥ 20; or 'sedentary' or 'standing' work if their total leisure activity score was ≥ 30. This resulted in exclusion of approximately 30% of those screened, a figure that matches well with the proportion of the UK population designated as active in prevalence surveys [37].

#### Study requirements

To fulfil measurement requirements participants had to be able to walk briskly, without help, on the flat for 15 minutes. Participants also had to live within reach of the measurement centre and the Family Health Facilitators; defined as a 30-minute average travel time from the study co-ordination centre. Other exclusion criteria included individuals with serious physical or psychiatric illness limiting programme involvement; people with life issues interfering with the study; those known to be pregnant or have diabetes before baseline measurement; and those planning to move away. As shown in Figure 1, application of these criteria reduced the 837 'interested' responses to 465 potentially eligible individuals, who were telephoned by a trained interviewer to confirm eligibility. Eligible and interested individuals were then scheduled for baseline measurement at either the Ely Research Centre or the Addenbrooke's Hospital Wellcome Trust Clinical Research Facility, where written consent was obtained.

Eligible offspring were registered with general practitioners in the Eastern Region of the UK. Prior to both baseline measures and randomisation, these doctors were individually informed about their registered patients' intention to participate in ***ProActive***. Brief details of the trial were sent, together with a request for feedback if the practitioner had any concerns about the offspring's participation, or about the safety of the facilitators making home visits.

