### Randomisation

Randomisation was carried out centrally by the trial statistician, using a partial minimisation procedure that dynamically adjusted the randomisation probabilities in order to balance important covariates; body mass index, sex, age, physical activity (individually calibrated heart rate monitoring, see below), family size, and behavioural intentions. Randomisation thus used baseline measures. Thirty-two pairs of siblings and two sibling-triples were cluster randomised to the same study group to avoid contamination, and the remaining 295 participants (81%) were individually randomised. Overall, 365/465 (78%) of those eligible went forward to randomisation.

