### Baseline measures and follow-up

At baseline and the end of the study, all participants attend the study centre at either Ely or Cambridge for questionnaires, physiological and anthropometrical measures, and venesection. At six months, psychological and self-reported physical activity data are collected by postal questionnaires. Measures relating to the intervention programme evaluation are collected by the facilitators during the intervention, and we assess reported use of self-regulatory strategies by participants to increase their activity levels at six and twelve months.

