### Measurement

The distribution of measures across baseline, six-month and one-year follow-up are shown in Table 1. The principle outcome is an objective measurement of physical activity energy expenditure, the daytime physical activity ratio (dayPAR), which is the ratio of daytime energy expenditure to resting energy expenditure measured using heart rate monitoring with individual calibration for the heart rate-energy expenditure relationship [40,41]. This allows more precise quantification of the relationship between energy expenditure and relevant disease end points than self-report [13]. The method has been validated against the gold standard techniques of doubly-labelled water and whole-body calorimetry [42]. Physical activity is also measured by a validated questionnaire covering work, recreation and domestic activity over the previous month and year [43], and offspring report of usual physical activity patterns among family members and how they changed over the previous year.

**Table 1 T1:** Study measures

**Measures**	**Baseline**	**6 months**	**12 months**

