### Data management, quality assurance and exclusion of bias

Physiological and anthropometric measures are made in two centres by observers unaware of individuals' group allocation. Biochemical measures are made in one laboratory with established quality assurance systems. Randomisation was undertaken by the trial statistician, independently of the trial co-ordination team, and the data entry team are unaware of study group.

The administrative database (participant information), dayPAR values and blood test results are managed in-house, with the latter being double entered. Numeric fields have limiters set so that values outside a defined range cannot be entered. Additionally, any blood results outside the 'normal range' are flagged for confirmation of value. Random checks on administrative data are performed regularly, checking the data on the database against paper records and correcting any errors found.

Double data entry of all anthropometric and questionnaire measures is undertaken by an experienced, independent agency, blind to study group (Wyman Dillon Research and Data Management, Bristol, UK). In addition, random checks are applied as described above.

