Main analyses will be at one year, comparing combined 'face-to-face' and 'distance' versions of the intervention programme with 'brief advice', comparing 'face-to-face' with 'distance' modes of the intervention programme, and estimating the difference between each intervention programme group and 'brief advice' to inform a larger pragmatic trial. Analysis by intention-to-treat will retain individuals within their randomised group regardless of participation. Comparisons will involve an adjustment for baseline physical activity and other variables used in the randomisation. We will undertake sensitivity analyses, assuming a range of potential outcomes for non-completers, informed by available baseline and interim data on non-completers. Non-completers will have multiple data imputed with a 'missing at random' assumption and with sensitivity analyses to represent optimistic and pessimistic scenarios for drop out. Clustering effects by family will be estimated for the primary outcome.

A secondary 'dose-response' analysis will use all three randomised groups, over baseline, six months and one year. A 'per protocol' analysis will also be undertaken among those completing the intervention programme.

The incremental cost of delivering the 'face-to-face' intervention programme will be compared to the 'distance' and 'brief advice' groups.

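### dayPAR and the other physiological outcomes are measured at two centres, but the stated covariate rule leaves measurement centre out: a small, avoidable loss of efficiency, not a bias

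*Protocol article*

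**What the plan says.** Under Study requirements, eligible people are "scheduled for baseline measurement at either the Ely Research Centre or the Addenbrooke's Hospital Wellcome Trust Clinical Research Facility". Baseline measures and follow-up covers both the baseline and the end-of-study visit: "all participants attend the study centre at either Ely or Cambridge for questionnaires, physiological and anthropometrical measures, and venesection". The section on data management and exclusion of bias confirms that "Physiological and anthropometric measures are made in two centres by observers unaware of individuals' group allocation". By contrast, it places the biochemistry in a single laboratory.

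The Measurement section defines the primary outcome, dayPAR, from "heart rate monitoring with individual calibration for the heart rate-energy expenditure relationship". Table 1 lists the dayPAR parameters among the physiological measures.

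The Randomisation section names six minimisation variables: "body mass index, sex, age, physical activity (individually calibrated heart rate monitoring, see below), family size, and behavioural intentions". Measurement centre is not among them. The analysis paragraph that follows the sample size calculation then fixes the covariates by reference to that list: "Comparisons will involve an adjustment for baseline physical activity and other variables used in the randomisation".

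**The concern.** Two sites carrying out treadmill tests and indirect calorimetry may read slightly differently. Blinding the observers stops measurement from differing by arm. It does not remove a constant offset between sites.

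The usual remedy is a site term in the model, and the covariate rule as written does not include one. An analysis that followed it would leave centre out. One that added centre later, after a difference had been seen, would be making an unplanned model choice. At stake is some avoidable residual variance in dayPAR and in the other physiological and anthropometric outcomes, in a trial whose power is already just under its nominal 80%.

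**Working it through.** **Inputs from the article (Sample size).** Residual SD 0.53; 100 completers per group, so 200 v 100 for the combined comparison; target difference 0.18; two-sided 5%; stated power 80%.

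**Assumed, because the article gives no figure.** Centre offset d = 0.1, 0.2 or 0.3 dayPAR; half the participants at each centre (the split that maximises the effect); slope of one-year on baseline dayPAR b = 0.4 to 0.6, held fixed; 0.53 contains no centre variance. Sibling clustering is ignored, as in the article's own calculation.

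**Reproducing the stated power.** SE = 0.53 × √(1/200 + 1/100) = 0.0649. Power = Φ(0.18/0.0649 − 1.96) = 79.2%, which agrees with the stated 80% to within a point.

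**Adding a centre offset.** With a 50:50 split, a centre indicator has variance 1/4.

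- Same centre at both visits: the offset is also in baseline dayPAR, and adjustment removes the fraction b. Residual SD = √(0.53² + (d(1 − b))²/4).
- Centre varying independently between visits: residual SD = √(0.53² + (d²/4)(1 + b²)).

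Example, same centre, d = 0.3, b = 0.4: √(0.2809 + 0.0081) = 0.5376, SE 0.0658, power 78.1%.
Example, independent centres, d = 0.3, b = 0.6: √(0.2809 + 0.0306) = 0.5581, SE 0.0684, power 75.0%.

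| Offset d | Power, same centre | Power, independent centres |
|---|---|---|
| none | 79.2% | 79.2% |
| 0.1 | 79.1% | 78.7–78.8% |
| 0.2 | 78.7–79.0% | 77.3–77.6% |
| 0.3 | 78.1–78.7% | 75.0–75.6% |

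**What a baseline-centre term recovers.** If participants keep their centre, the term removes the remaining offset and power returns to 79.2%. If centres vary independently, it removes only the b²d²/4 part. Residual SD is then √(0.53² + d²/4), giving 78.8%, 77.8% and 76.1% for d = 0.1, 0.2 and 0.3. The rest depends on centre at one year.

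**If 0.53 already contains a centre component of d²/4.** The residual SD without it is √(0.53² − d²/4). Removing that component in full would raise power above 79.2%, to 79.5%, 80.6% and 82.4%.

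**Chance imbalance in centre mix.** The SE of the difference in centre share is √(0.25 × (1/200 + 1/100)) = 0.061. An imbalance of two SEs is about 12 percentage points. With independent centres it moves the estimate by d × 0.122 = 0.012, 0.024 or 0.037. With the same centre it moves it by d(1 − b) × 0.122, or 0.005–0.007, 0.010–0.015 or 0.015–0.022. A one-SE imbalance moves it half as far.

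**The case against.** The strongest reply is that nothing in the article shows a centre difference, and two of the three assumed offsets exceed the whole target effect of 0.18. At d = 0.1 the loss is half a point or less either way. dayPAR is moreover a ratio of two measured quantities, so a proportional calorimeter error common to both would largely cancel. All of this stands, and it is why the point is minor.

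A reader might infer that participants may move freely between centres. The text does not support that. It names two sites and is silent on whether a person stays with one, and booking practice is operational detail that an article may leave to the full protocol. The larger losses in the table therefore illustrate an unconfirmed case.

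A reader might also infer that an imbalance in centre mix biases the treatment effect. It does not. Observers are blind and nothing ties centre to arm, so imbalance is random error. Centre variance left in the residual widens the standard error, which covers it. The same is true of any covariate left out of a model.

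Finally, the covariate sentence need not be exhaustive, and an analysis plan could add centre. That is so. But the sentence defines the set by reference to the randomisation variables, and centre is not one of them, so the published rule as written leaves it out.

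**Conclusion.** The point holds as a low-severity improvement. Two centres produce the primary outcome, and the stated covariate rule omits centre. If participants return to the same centre, the loss is about 1 point of power or less, even at an offset of 0.3. If centre varies independently between visits, it is about half a point at an offset of 0.1 and about 4 points at 0.3. These figures rest on assumed offsets, an assumed even split and an assumed slope; the article gives none of them.

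The primary comparison stays valid, with no systematic bias and no inflated type I error. Leaving centre out of the minimisation is not itself a fault that needs repair: recruitment has closed, and adjustment in the analysis is enough.

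**What to change.** In the analysis paragraph of Statistical procedures, add measurement centre at baseline to the prespecified covariates for dayPAR and the other physiological and anthropometric outcomes, and include it in the imputation model for non-completers. Baseline centre is fixed before randomisation, should already be on record for every participant, and costs one degree of freedom.

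Centre at one year should not go into the main model. It is determined after randomisation and does not exist for the non-completers whose outcomes are to be imputed. Where it differs from baseline centre, a sensitivity analysis among those measured can include it. That is also where most of the loss would be recovered if switching proved common.
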